### Population

The DEFIDIAG study will be conducted in 15 clinical genetic centers in France. All patients consulting a geneticist in one of the participating centers will be screened for eligibility. The study will include children or adults with ID of unknown etiology (index cases or probands), whatever the severity (but with proven ID by ad hoc neuropsychological testing in patients in whom ID is clinically questionable), and whatever the associated manifestations. Individuals with an obvious ID syndrome with a well-known molecular diagnosis will not be considered for inclusion. Children aged between 0 and 5 years will only be considered for inclusion in case of severely delayed development in terms of motor skills, language, and/or sociability. Patients and both biological parents are included if they confirm their willingness to comply with all the study procedures, their availability for the duration of the study, and sign the appropriate consent forms.

Non-inclusion criteria include: isolated learning disabilities; no possibility of obtaining a blood sample from both biological parents; any in the patient condition that, in the investigator’s opinion, would jeopardize compliance with the protocol; one or both parents with ID; parent placed under judicial protection (guardianship, curatorship, tutorship).

The strategy based on GST is expected to yield a diagnosis in at least 60% of patients with ID versus 30% with the reference minimal strategy in the population of patients attending for a first genetic investigation (never-explored patients). However, the strategies will be compared in 7 subgroups: 1) 3 defined by age: children <2 years old/2–5 years/>5 years; 2) 4 subgroups of patients defined according the severity of ID, and/or 3) with associated manifestations:1) mild ID associated with another sign, 2) moderate to severe ID, 3) ID with major non-cerebral abnormality, and 4) ID associated with epilepsy The smallest sub-group (subjects with mild ID associated with another significant sign) should represent around 15% of the total population, and the difference between the GST and the reference strategy in this particular subgroup can be assumed to be less than 15%. In addition, it is assumed that fewer than 1% of diagnoses identified with the referral minimal strategy will not be identified by the GST. Finally, we will also compare GST and GSS in a subgroup of randomized patients referred for the first time. For this specific comparison, a difference of 7% is expected, and <0.1% of diagnoses identified by GSS and not by GST. Considering these 9 planned comparisons (8 comparisons between GST and the reference strategy and 1 between GST and GS), the one-sided alpha risk is fixed at 0.00278. Based on these hypotheses, and a power of 80%, among patients seen for a first genetic investigation (50% of the population to be recruited), 41 patients are required for the main comparison, and 91 patients with mild ID + other syndrome are necessary. To recruit this number of patients, we estimate that it will be necessary to screen 607 patients attending for a first referral. A subgroup of 196 patients will be randomized to undergo GSS in addition to GST plus the reference minimal strategy. The sample size for this subgroup will be sufficient to compare GST and GSS in terms of diagnostic yield, as well as in terms of efficiency (a sample size over 150 is usually deemed sufficient). As we intend to include 50% of patients attending for a first genetics evaluation (never-explored patients), and 50% of patients who have already been investigated (previously-explored patients), a total of 1,214 patients are necessary. Considering that approximately 5% of samples will not be analyzable, it will therefore be necessary to include 1,275 index cases plus both their parents, for a total of 3,825 participants.

The qualitative study will be performed in a sub-sample of the overall population, in two centres. In order to maximize the scientific rigor of the study and to alleviate the potential burden resulting from the interviews, whilst fostering discussions between the sociological and psychological sides, we chose to separate the interview procedures into two groups. For the psychological sub-study, 15 interviews with parents will be conducted at each assessment timepoint (T1, T2, T3), giving a total of 45 interviews. For the sociological sub-study, 15 interviews with parents will be conducted at each assessment timepoint (T1, T2, T3), giving a total of 45 interviews. A total of 15 interviews per assessment timepoint was chosen to achieve data saturation, a key concept of qualitative analysis, namely the point beyond which further interviews do not yield any new information (Glaser and Strauss, 1967). As far as possible, the study populations of patients and parents will be stratified into two subgroups, namely never-explored, and previously-explored patients. The subgroups of parents will also be stratified according to the clinical profile of the patients (mild vs moderate or severe ID).

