#### Genomic Circuit

All blood samples received for the DEFIDIAG study by the reference laboratory are extracted using a method previously validated by the sequencing platform (Centre National de Recherche en Génomique Humaine, CNRGH). This validation step was performed on the same blood sample, and genomic sequences obtained after various DNA extraction methods were compared by the CNRGH in terms of global DNA quality, mean coverage and SNV/CNV detection. In all, five extractions methods were validated (three automatic and two manual). After blood extraction, 3 µg DNA aliquots labelled with an anonymous barcode are sent to the CNRGH *via* a courier at room temperature. Several quality controls are then performed before the sequencing step (fluorimetric DNA quantification, quality measurement using the DNA integrity number, PCR amplification test, and sex control). If DNA of the trio is accepted, 1.1 µg of DNA is fragmented using an optimized CNRGH GS protocol. The GS is optimized in order to reach a mean coverage of 30X for each sample; a minimum of 25X mean coverage is required. Below these specifications, the sequencing is considered as a failure and will not be repeated.

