### Quality Controls

Several quality controls are carried out before biological analysis: genome mean coverage over 25X is required for the trio; sex verification (SRY detection) and trio concordance (<1% of Mendelian error transmission in trio using Plink software) are checked before interpretation.

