#### Statistical Analyses

The percentage of ID causal diagnosis identified will be compared between strategies (GST vs reference strategy) using a McNemar test in the overall first-investigation population, then in the seven subgroups of interest. To account for multiple testing, the unilateral alpha risk is set at 0.00278, and also for the secondary comparisons of the diagnostic yield of GST vs. GSS, which will be performed in the dedicated randomized subgroup.

McNemar tests (unilateral alpha risk set at 0.025) will also be used to compare the percentage of causal diagnoses identified by GS and reference strategies in the sub-groups of the individuals coming for a first genetic referral without major non-cerebral abnormality or without epilepsy. This test will also be used in the overall population (first-investigation patients and previously investigated patients) to compare the percentage of causal diagnoses identified by GS strategies in patients with negative CMA. The percentage of causal structural changes identified by GST vs the reference minimal strategy will also be compared using McNemar tests in the first-investigation population (firstly considered all together, and then stratified by subgroups). The number and type of consistent and divergent variants identified with CMA and GS strategies will also be described. The frequency and characteristics of the situations where the causal diagnosis is identified by the reference strategy but not by the GS analyses will be described, as well as the frequency and characteristics of situations where the causal diagnostic is made by GSS and not by GST.

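### The trial is sized on a mild-ID difference worded as a ceiling (below 15 points), so the stated 80% power there is not assured; the 5% loss allowance is also 3 index cases short and its unit is unclear

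*Protocol article*

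**What the plan says.** All the sample-size figures are in the Population section of the protocol article.

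- **Alpha.** "Considering these 9 planned comparisons (8 comparisons between GST and the reference strategy and 1 between GST and GS", and so "the one-sided alpha risk is fixed at 0.00278", which is 0.025/9.
- **Main comparison.** GST is expected to diagnose at least 60% of patients against 30% for the reference strategy; 41 patients are required.
- **Smallest subgroup.** Mild ID plus another significant sign is put at around 15% of the population, and "the difference between the GST and the reference strategy in this particular subgroup can be assumed to be less than 15" per cent.
- **Reverse discordance.** Fewer than 1% of the reference strategy's diagnoses are assumed to be missed by GST.
- **Result.** "Based on these hypotheses, and a power of 80" per cent, 91 subgroup patients are needed, which leads to 607 first referrals and, with equal numbers of previously investigated patients, to 1,214.
- **Loss.** "Considering that approximately 5% of samples will not be analyzable, it will therefore be necessary to include 1,275 index cases plus both their parents".

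Statistical Analyses names the test: GST and the reference strategy are compared "using a McNemar test in the overall first-investigation population, then in the seven subgroups of interest".

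Two other sections bear on the loss. Genomic Circuit says of samples with insufficient coverage: "Below these specifications, the sequencing is considered as a failure and will not be repeated". Quality Controls adds that "genome mean coverage over 25X is required for the trio".

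**The concern.** The difference used for sizing should be a planned value or a minimum worth detecting. Here it is worded as an upper limit. Read as written, the plan expects a smaller effect than the one it is powered for, in the one subgroup that sets the size of the trial. The main comparison is worded the other way, with a yield of at least 60%.

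The loss allowance raises two further questions: whether the inflation was done correctly, and whether the 5% refers to families or to individual blood samples. GST needs three acceptable samples per family.

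The stake is how a non-significant result in mild ID will be read. The study aims to identify the most appropriate strategy by clinical presentation. A reader who trusts the 80% may take such a result as evidence that GST adds little in mild ID, when the test may have had much less power.

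**Working it through.** **Inputs.** One-sided alpha 0.00278, power 80%, subgroup share 15%, loss 5%, and the McNemar test, all from the protocol article. The article does not say whether the test is exact or asymptotic, so I checked which form returns its figures.

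**Formula.** Let d be the difference, p01 the share of patients diagnosed by the reference strategy only, and p10 = d + p01 the share diagnosed by GST only. Given m discordant pairs, the exact test rejects when the GST-only count reaches c(m), the smallest c with P(Bin(m, 1/2) >= c) <= 0.00278. Then

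power = sum over m of P(Bin(n, p10 + p01) = m) x P(Bin(m, p10/(p10 + p01)) >= c(m)).

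**Step 1: reproduce the plan's figures.**

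- Main comparison, d = 30 points, p01 = 1% (cells 31%/1%): n = 40 gives 78.9%, n = 41 gives 80.9%. The plan says 41.
- Subgroup, d = 15 points, p01 = 1% (cells 16%/1%): n = 90 gives 79.5%, n = 91 gives 80.3%. The plan says 91.
- Asymptotic formulas with the same cells do not match: Connor gives 44 and 96, Miettinen 37 and 82.

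The two exact matches indicate that the design values were exactly 15 points and 1% of patients. The rest of the chain is 91/0.15 = 606.7, so 607; 607 x 2 = 1,214; 1,214 x 1.05 = 1,274.7, so 1,275.

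**Step 2: power of n = 91 below 15 points.** The 1% is also worded as a ceiling, so p01 is varied too. Taken literally it is 1% of reference diagnoses; at the 30% reference yield that is 0.01 x 30% = 0.3% of patients. The 30% is given for first referrals as a whole, so using it in the subgroup is an assumption.

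| Reverse cell p01 | 15 points | 14 | 13 | 12 | 10 |
|---|---|---|---|---|---|
| 1% | 80.3% | 74.2% | 67.1% | 59.0% | 40.8% |
| 0.5% | 86.5% | 81.3% | 74.9% | 67.0% | 47.5% |
| 0.3% | 89.4% | 84.7% | 78.6% | 70.9% | 50.8% |
| 0% | 94.2% | 90.5% | 85.2% | 77.8% | 56.5% |

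With p01 = 1%, 80% power needs 99 patients at 14 points, 108 at 13, 119 at 12 and 148 at 10.

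**Step 3: inflation for loss.** To keep 1,214 after a 5% loss, 1,214/0.95 = 1,277.9, so 1,278. The plan's 1,275 leaves 1,275 x 0.95 = 1,211. The expected subgroup is 1,275 x 0.95 x 0.5 x 0.15 = 90.8 patients instead of 91, so power stays at about 80%.

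**Step 4: unit of the 5%.**

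- Per index case or trio: as in step 3, with no material shortfall.
- Per individual sample, with independent failures within a family (an assumption): 0.95^3 = 0.857 of trios survive. Then 1,275 x 0.857 = 1,093 trios, 547 first referrals and 547 x 0.15 = 82 subgroup patients. Power at 15 points is 72.3% with p01 = 1% and 82.7% with p01 = 0.3%. Keeping 1,214 trios would need 1,214/0.857375 = 1,416 index cases.

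**The case against.** The strongest reply is that the plan's arithmetic is right at its design point: both 41 and 91 reproduce exactly. A reader might infer from the wording that 80% power is simply not delivered in mild ID. The document does not support that. The 1% reverse discordance is a ceiling as well, and one cannot take one ceiling literally while holding the other at its worst value. At a 0.3% reverse cell, 91 patients still give 85% power at 14 points. This stands, but it helps only close to 15 points: at 12 points power is 71% at 0.3%, and 78% even with no reverse discordance at all. Nothing in the document says that the difference is as small as 12 points, and nothing rules it out.

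A reader might also infer that 1 - 0.95^3 = 14.3% of trios will be lost and that the power is really about 72%. That too goes beyond the text. The 5% is applied to 1,214 patients to give index cases, and parents are added only afterwards, which suggests a loss per family. The 72% needs a per-sample rate, independent failures and a 1% reverse cell together; with a 0.3% cell, 82 patients still give 83% at 15 points. What remains is that the text says samples, that the whole trio must pass, and that failed sequencing is not repeated. The unit therefore needs stating.

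Finally, this is one of seven secondary subgroup comparisons, and the document contains no rule that treats a non-significant subgroup result as absence of benefit. That limits the weight of the point.

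**Conclusion.** The point holds as a defect in how the design value is stated. The figure of 91 is correct for a 15-point difference with 1% reverse discordance, but the text makes 15 points an upper limit. Below it the stated 80% is not assured: 74% at 14 points, 59% at 12 and 41% at 10 with a 1% reverse cell, or 85%, 71% and 51% with 0.3%. These figures assume the exact test, which is inferred from its reproducing both of the plan's sample sizes. Whether the ceiling is a slip of wording cannot be told from the document; either way the sentence does not support the number.

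The inflation error is certain but small: 3 index cases and about 0.2 subgroup patients. The per-sample shortfall is conditional and is a request for clarification.

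The primary comparison is untouched. It needs 41 patients and would have about 547 to 606 analysable first referrals under either reading of the loss. This is a minor to moderate correction.

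**What to change.** 1. State the subgroup difference as a planned or minimum value (at least 15 points) and the reverse cell used as 1% of patients. Say that the 80% holds at those values.
2. Give the power of 91 patients at 10, 12 and 15 points: 41%, 59% and 80% with the 1% cell, and 51%, 71% and 89% if 0.3% is thought realistic.
3. Replace 1,275 by 1,278, or keep 1,275 and say that it yields about 1,211 analysable index cases. If it is replaced, the participant total becomes 3 x 1,278 = 3,834 instead of 3,825.
4. State whether the 5% is per index case (trio) or per individual sample. With 955 patients included at the date given under Trial Status, the observed failure rate per trio could be reported. Only if the rate proves to be per sample, with independent failures, should the stated subgroup power be lowered, to about 72% at 15 points with a 1% reverse cell or 83% with 0.3%.

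The cost is a few sentences and at most 3 more index cases. The subgroup power will look less favourable at differences under 15 points. Resizing is not required by this point: for scale, 80% power at 12 points with a 1% cell would take 119 subgroup patients, hence 794 first referrals, 1,588 patients and 1,588/0.95 = 1,672 index cases.

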### Study Conduct

#### Inclusion

During a genetics consultation and after verifying the inclusion and non-inclusion criteria, the patient and both parents will be informed about the study by the investigators and invited to participate. If they agree either during the visit or after a period of reflection, they will be invited to sign the consent form. During this visit, the history of the illness, family history, the examinations already carried out and the corresponding results will be collected with the assistance of a Clinical Research Technician (CRT) in the dedicated e-CRF prepared by the DEFIDIAG methodology and management center (INSERM Clinical Investigation Center—Clinical Epidemiology Unit CIC-EC1432), using CleanWEB software (Telemedecine technologies SAS, Boulogne-Billancourt, France). If necessary, the clinical geneticist will prescribe additional neuropsychological tests. A blood sample (5 ml -EDTA tubes) will be obtained from each participant (patients with ID as well as both biological parents). These blood samples will be sent to the reference DEFIDIAG laboratory of the center (Figure 2, Supplementary Table S1) in compliance with regulations for the shipment of diagnostic samples (category B). A diary will be given to the family where they will be asked to note the patients’ use of healthcare and medico-social services until the return of the GS results. This diary makes it possible to collect the medical examinations, biological investigations, rehabilitation and psychological consultations as well as the medico-social follow-up. A follow-up by phone will be performed every 3 months by the CRT in order to guarantee the completeness of the collection.

For parents/patients willing to participate in the qualitative study in the two centers conducting this part of the study, additional data concerning the familial situation, the number of children, the social deprivation level and the existence of informal and/or professional caregivers at home will be collected, as well as the contact details and address of the participants, for the sociologist or psychologist to organize the interview.

#### Genomic Circuit

All blood samples received for the DEFIDIAG study by the reference laboratory are extracted using a method previously validated by the sequencing platform (Centre National de Recherche en Génomique Humaine, CNRGH). This validation step was performed on the same blood sample, and genomic sequences obtained after various DNA extraction methods were compared by the CNRGH in terms of global DNA quality, mean coverage and SNV/CNV detection. In all, five extractions methods were validated (three automatic and two manual). After blood extraction, 3 µg DNA aliquots labelled with an anonymous barcode are sent to the CNRGH *via* a courier at room temperature. Several quality controls are then performed before the sequencing step (fluorimetric DNA quantification, quality measurement using the DNA integrity number, PCR amplification test, and sex control). If DNA of the trio is accepted, 1.1 µg of DNA is fragmented using an optimized CNRGH GS protocol. The GS is optimized in order to reach a mean coverage of 30X for each sample; a minimum of 25X mean coverage is required. Below these specifications, the sequencing is considered as a failure and will not be repeated.

### Variant Calling

Whole genomic sequences are analyzed by two separate SV and SNV/indel pipelines developed and validated by the CNRGH sequencing platform and IMAGINE bioinformatics team. Briefly, the raw data will be produced as compressed FASTQ files generated from the. bcl files by the CNRGH sequencing platform. The sequences are aligned to the human reference genome GRCh37 using the Burrows-Wheeler Aligner BWA software (Li and Durbin, 2010) and made available as BAM files. Aligned sequences are sorted, cleaned and the PCR duplicates are marked using the Sambamba software (Tarasov et al., 2015) in order to eliminate most of the NGS’ well-known biases. A local realignment of the sequences around insertion and deletion sites and the base quality recalibration is performed using GATK (McKenna et al., 2010). After sequence quality control and alignment of the reference genome, the CNRGH performs the variant calling on the entire genome for the Single Nucleotide Variants (SNV), small insertion/deletions (indels) and structural variants (including Copy Number Variant, CNV). SNV and indel calling are performed using the Haplotype Caller from GATK software in “bp resolution” mode to produce gVCF files. Imbalanced SV (CNV) detection > 1 kb is performed using three different softwares: Wisecondor (Raman et al., 2019), Canvas (Roller et al., 2016) and Manta (Chen et al., 2016). Balanced SV (translocation, inversion) detection is done using Manta software. Results are produced in the format of a VCF file to match the common file standard format in NGS analysis. These files are then collected by the IMAGINE Polyweb platform: additional combined TRIO gVCF analysis (genotypeGvcf) and CNV Wisecondor analysis will also be performed.

### Quality Controls

Several quality controls are carried out before biological analysis: genome mean coverage over 25X is required for the trio; sex verification (SRY detection) and trio concordance (<1% of Mendelian error transmission in trio using Plink software) are checked before interpretation.

### Biological Analysis

The .vcf and .bam files are implemented in Polyweb software developed and previously validated by the IMAGINE bioinformatics platform. This software makes it possible to annotate, analyse and visualise all the genomic variations in two different web interfaces Polyviewer (for SNV, small indel, exonic deletion or duplication) and Polycyto (for balanced and unbalanced SV) of all human genes in trio or solo analysis. Moreover, a specific ID44 bioinformatic gene panel will make it possible to study variations from this gene list. Read variations are visualized using IGV software (Robinson et al., 2011).1) SNV/indel analysis

The polyviewer interface gives access to several annotations, such as patient and trio sequencing data (number of mutated and total reads), data from common free-access databases (GnomAD (Karczewski et al., 2020), Clinvar (Landrum et al., 2020), OMIM (Amberger et al., 2019), GenCode (Frankish et al., 2019) …), licensed database HGMDpro and also internal databases (Déjà Vu), gene or protein predicted impact, splice prediction [SpliceAI (Jaganathan et al., 2019)], and for trio analysis, inheritance status of the variation. Our objective is not to evaluate the value of GS for early detection of ID, but rather, to evaluate the risk/benefit of GS for the etiological diagnosis in already-identified ID. The internal database (Déjà Vu) contained over 20.000 exomes, 50.000 panels and 1,000 genomes for SNV/Indel variations with differentiation between ID and non-ID patients.

The following filtration keys are applied to focus on potentially pathogenic variations: GnomAD allele count<1,000, GnomAD homozygote count< 5, and predicted protein impact onto all gene transcripts (Stop gain, Stop loss, Start loss, frameshift, in frame deletions or insertions, missense, and predicted splice region, Déjà Vu for patients non ID < 1,000 and homozygote count < 5).

Ranking of identified variations is then performed based on internal Polyweb criteria: variation sequence quality, *de novo* status if available, known ID gene or OMIM gene, protein or splicing impact prediction, gene with AR inheritance and homozygous or compound heterozygous variations, male and X linked variation, known pathogenic variations in HGMDpro or ClinVar, frequency in GnomAD.

Those criteria will ensure that all variations are analyzed from all known human genes (OMIM or not) that are predicted to affect proteins.2) SV analysis

The polycyto interface gives access to several annotations using AnnotSV software (Geoffroy et al., 2018), DGV, OMIM and internal Déjà Vu databases. The internal SV database (Déjà Vu) contained at the beginning of the project 200 Novaseq sequenced genomes from non-ID patients. The number of genomes in Déjà Vu is now up to 2000 (mostly ID patients).

Ranking of identified variations is based on calling quality and inheritance status. For balanced SV (translocation and inversion) a greater weight is given to variations whose break points are found in OMIM genes.

After filtering CNV already detected at least 10 times in the Déjà Vu database, all detected CNV are analyzed using standard criteria [ACMG recommendations (Riggs et al., 2020)]. For Déjà Vu count, two CNV are considered identical if they overlap over 75% of their reciprocal length. For balanced SV (translocation and inversion), break points must have an identical genomic position ± 50bp.

All imbalanced and balanced SV are checked in IGV software by visualizing paired read alignment anomalies (insert size, pair orientation and split read). In addition, for CNV, allele frequency plots ranked according to chromosomal positions are also available.

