This DEFIDIAG pilot study focuses on intellectual disability (ID), as one of the most challenging models of rare disease. ID affects around 1–3% of the general population, with around 15 per 1,000 persons having mild ID and around 3 per 1,000 having severe ID. It is the most common cause of referral to pediatric genetic centers. ID results from abnormal brain development due to numerous possible cellular processes, including neuron proliferation and differentiation, neuron or astrocyte metabolism and maintenance, neurotransmitter synthesis, receptor or signal transduction, transcriptional and translational control. It is also well recognized that ID may result from non-genetic causes (neonatal anoxia, toxic effects, deprivation … ) or from genetic causes. Gene and chromosomal variations involved in human ID are numerous and include recurrent chromosomal events from complete chromosomal duplication, segmental chromosomal duplication or deletion, or small genic variations altering the function one among more than 1,500 genes such as single nucleotide variants (SNV), insertions or deletions (indel), unbalanced (CNV) or balanced structural variants (SV) in coding or non-coding regions, or even rarer events such as repeat expansions, uniparental disomy, mobile element insertion etc., which are reported in the OMIM registry. Approximately 15% of ID is attributable to cytogenetically clear-cut abnormalities, with at least two-thirds of these cases accounted for by trisomy 21 (Ellison et al., 2013) and up to 40% to one variation in one of the 1500 ID gene when exome sequencing is performed (Han and Lee, 2020).

Before next generation sequencing methods, genetic testing was limited to traditional karyotype and fragile X analysis, sometimes with gene specific Sanger analysis, when a specific syndromic ID was suspected. In the past 10 years, microarray analysis (CMA) has been widely used for the genetic diagnosis of ID. NGS tests recently emerged, in the last 5 years, with gene panel approaches and Whole Exome Sequencing (ES) following CMA and fragile X syndrome screening. Today, the question arises about the input of whole genome sequencing as a first approach in such patients, as this may profoundly modify the testing process by replacing CMA and other sequencing approaches (specific genes, panel, ES) and in addition, may detect new molecular mechanisms not detectable by CMA and ES.

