### Biological Interpretation

Biological interpretation follows standard criteria [ACMG recommendations (Richards et al., 2015; Riggs et al., 2020)]. Briefly, balanced and imbalanced SV and SNV/Indel/Small exonic deletions, or duplications are all performed by two independent biologists. All variations are checked on. bam data and doubtful variations are confirmed using standard molecular analysis before biological analysis (less than 10 mutated reads for SNV, doubtful *de novo* status, doubtful deletion, duplication or translocation/inversion … ).

For CNV (duplication, deletion), current cytogenetic analysis is performed based on DGV, inheritance mode, recurrency, and gene contents. For balanced SV, only variations disrupting a known ID gene are retained for interpretation. Small SNV/indel are analyzed following mendelian modes of transmission (*de novo* AD or X linked variations, transmitted AD variation in case of known incomplete penetrance or suspected parental mosaic, maternally X transmission in male patients, homozygous or compound heterozygous variations (SNV or CNV) in autosomal recessive hypothesis). This broad approach ensures that co-occurring mutations (expected in about 5% of cases) will be identified (Yang et al., 2014).

Variants of interest are then recorded in the e-CRF and discussed during the MDM.

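### As written, the CNV recurrence filter counts hits in a database that is now mostly ID patients, so GST can lose the more frequent recurrent pathogenic CNVs in the comparison with CMA

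*Protocol article*

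**What the plan says.** All of the rule stands in the protocol article, Biological Analysis, under SV analysis.

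- Filter: "After filtering CNV already detected at least 10 times in the Déjà Vu database, all detected CNV are analyzed". The ACMG-based assessment comes after this step.
- Matching rule for the count: "two CNV are considered identical if they overlap over 75% of their reciprocal length".
- Database at the start: it "contained at the beginning of the project 200 Novaseq sequenced genomes from non-ID patients".
- Database at the time of writing: "The number of genomes in Déjà Vu is now up to 2000 (mostly ID patients").

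Under SNV/indel analysis in the same section, the internal database is described "for SNV/Indel variations with differentiation between ID and non-ID patients", and the filter key uses that split: "Déjà Vu for patients non ID < 1,000 and homozygote count < 5". No such split or restriction is stated for CNVs.

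The Introduction says that the known genetic causes of ID "include recurrent chromosomal events from complete chromosomal duplication, segmental chromosomal duplication or deletion". Under Biological Interpretation, for CNVs, "current cytogenetic analysis is performed based on DGV, inheritance mode, recurrency, and gene contents". Recurrence therefore informs interpretation, but only for CNVs that have passed the filter.

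**The concern.** A recurrence filter rests on the premise that a variant seen often is probably benign. That holds when the count is taken in unaffected people. In a database made up mostly of ID patients, a CNV may be frequent because it causes ID. Recurrent CNVs with similar boundaries are also the ones most likely to meet the 75% reciprocal-overlap rule, so their counts pool.

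Three features make this matter for the comparison:

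- **It is one-sided against CMA.** CMA follows the routine care circuit, and no Déjà Vu filter is stated for it. The laboratories reading GS stay blinded to CMA, so a CMA finding would not bring a filtered CNV back into the GST read.
- **It drifts.** The cut-off is a count and the database grows, so a CNV could pass for a patient read early and be removed for one read late.
- **It touches a stated objective.** The article compares causal structural changes between GST and CMA, and will describe cases diagnosed by the reference strategy but not by GS. The sample-size paragraph in Population assumes that such cases make up fewer than 1% of reference diagnoses.

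GSS would be affected in the same way wherever the same filter is used.

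**Working it through.** The article states no expected CNV loss or CNV sensitivity, so there is no figure of its own to reproduce for the filter.

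**1. Effective cut-off**

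- At the start: 10/200 = 5% of non-ID genomes.
- Now: 10/2,000 = 0.5% of a mostly ID series.

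**2. Chance that one recurrent CNV is filtered**

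Let f be the fraction of contributing genomes that carry the CNV and N the number of those genomes. The chance of meeting the filter is P(X ≥ 10) with X ~ Binomial(N, f). The article gives no f for any CNV, so 0.1% to 1% is an assumed range. It gives only an upper figure for the database and the word mostly, so N runs from a bare majority (1,001) to 2,000.

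| f | N = 200 | N = 1,001 | N = 1,500 | N = 2,000 |
|---|---|---|---|---|
| 0.1% | about 0 | about 0 | about 0 | 0.005% |
| 0.2% | about 0 | about 0 | 0.1% | 0.8% |
| 0.3% | about 0 | 0.1% | 2% | 8% |
| 0.5% | about 0 | 3% | 22% | 54% |
| 0.75% | about 0 | 22% | 69% | 93% |
| 1% | about 0 | 54% | 93% | 99.5% |

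At f = 0.5% and N = 200 the chance is about 1 in 10 million. The filter was harmless to such CNVs in the starting database. It is a material risk now only for the more frequent ones.

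**3. What a loss would do to discordance**

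Assume that the filtered CNVs together account for 0.5% to 1% of the 607 never-explored patients and that CMA would have found them.

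- Lost by GST: 607 × 0.005 = 3.0 to 607 × 0.01 = 6.1 patients.
- Expected reference diagnoses: 30% of 607, about 182.
- Share: 3.0/182 = 1.7% to 6.1/182 = 3.3%.

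Read as a share of reference diagnoses, this exceeds the assumed 1%. Read as a share of all patients (0.5% to 1%), it would use up much or all of that allowance.

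**4. What it would do to the primary comparison**

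One-sided McNemar sample size: n = [z(α)√ψ + z(power)√(ψ − d²)]² / d². Here ψ = p10 + p01, d = p10 − p01, z(α) = 2.773 for α = 0.00278, and z(power) = 0.842 for 80% power; p10 is GST-only and p01 reference-only.

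- Plan's case, d = 0.30: p01 = 0.5% gives 41.8 and p01 = 1% gives 43.2, close to the stated 41.
- Pessimistic loss of f from p10 as well as gain of f in p01, starting from 0.31 and 0.01: f = 0.5% gives 46.5 and f = 1% gives 50.1.

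Against 607 planned, the primary test remains amply powered.

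**The case against.** Several counter-arguments carry weight.

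- **The effect may be small.** At f of 0.2% or less, almost nothing is filtered even with 2,000 genomes, and with a bare ID majority f = 0.5% gives only 3%. The design may lower f further: half the index cases were already investigated without a diagnosis, and patients with an obvious syndrome are excluded. If these patients feed the database, CNVs that CMA detects would be depleted in it. The article does not say whether they do. This point stands and is why the full range is shown.
- **The pipeline may already be safe.** The harmonised laboratory protocol is not shown and may use non-ID counts or exempt known regions. This stands as a possibility, but the article gives the CNV rule in detail and includes the safeguard for SNVs alone.
- **The loss would be visible.** The plan describes divergent CMA and GS variants, and CMA results still reach families. That exposes discordance but does not correct the GST yield, nor does it separate a filter artefact from a limit of the technology.

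A reader might infer that the filter demonstrably produces false negatives on the GS side alone and threatens the primary result. The article does not support that. It shows a risk, not observed losses. The 44-gene arm of the reference strategy also comes from the GS data, including its CNV analysis, so only CMA is clearly outside this pipeline. A bias against GST cannot create a false claim of superiority, and the planned margin (60% versus 30%) is far larger than the loss considered here.

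**Conclusion.** The concern holds as a risk created by the rule as written. The CNV filter takes an unrestricted count in a growing, mostly ID database and is inconsistent with the SNV filter in the same section. Followed literally, it can remove the more frequent recurrent pathogenic CNVs before interpretation, increasingly as the database grows. This would bias the GST versus CMA structural comparison against GST and could add reference-positive, GST-negative cases.

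The size cannot be fixed from the article. It is negligible for CNVs carried by about 0.2% or fewer of contributing genomes. At 0.5% it ranges from 3% to 54%, depending on how many genomes contribute, and at 1% from 54% to 99.5%. These figures rest on assumed carrier fractions and on treating genomes as independent. The primary conclusion is unlikely to change. The point should be fixed for the sake of the secondary structural comparison and the discordance description.

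**What to change.** 1. Count CNV recurrence in non-ID genomes only, as the SNV filter already does, and name the fixed database version used.
2. Do not discard automatically any CNV that overlaps a known recurrent pathogenic region.
3. Re-apply the corrected filter to all genomes by one uniform rule, with readers still blinded to CMA. Send newly retained CNVs of interest to the multidisciplinary meeting.
4. Report the yield from the blinded read already made and from the re-filtered read separately. A second look on the GS side can only raise the GST yield, so it should not silently replace the read already made.
5. If the pipeline already counts non-ID carriers or exempts known regions, correct the sentence and state the database version; no re-read is then needed on this ground.

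Cost: a carrier-status flag in the database, re-filtering of existing variant files and more CNVs to read per case. The extra reading cannot be quantified from the article. No new samples are needed. With only 200 non-ID genomes documented, a count of 10 means a 5% cut-off, which is loose, but it is the one in force when the project began.
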